|                                                                                                                   |                                                                                                                             |                                                                                                       |
|-------------------------------------------------------------------------------------------------------------------|-----------------------------------------------------------------------------------------------------------------------------|-------------------------------------------------------------------------------------------------------|
| nurses, receptionists and pharmacists).                                                                           |                                                                                                                             |                                                                                                       |
| vi. To assess and understand the mechanisms of action of brief health related messages on self-reported adherence | vi. Change in quantitative process measures and relationship between changes in these measures and self-reported adherence. | vi. End of follow up period qualitative interviews/survey/telephone contacts with trial participants. |
| viii. To assess feasibility and acceptability of self-completion of the resource use questionnaire.               | vii. Proportion of completed resource use questionnaire.                                                                    | vii. End of follow-up period.                                                                         |
| Exploratory measures                                                                                              | viii. Changes in primary and secondary measures that will be used in the main trial.                                        | viii. Differences between time points obtained from baseline to 26 weeks.                             |
|                                                                                                                   | ix. Information on message delivery and interaction with participants.                                                      | ix. Automated reports from messaging service on messages delivered and interactive messaging          |

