### 3 TRIAL DESIGN

#### 3.1 Intervention study

This is a primary care based, multicentre, 2-year (including a 26-week intervention), two-arm individually (1:1 ratio) randomised controlled, parallel group feasibility trial.

Patients with type 2 diabetes will be randomised to current care with individually tailored mobile device-based intervention encouraging and supporting them in developing a habit of taking their medication as intended and providing hints and tips to help them with other aspects of living with the condition (treatment arm) or to current care with the addition of infrequent non-health related messages (usual care arm).

The trial team will be blinded as to participant allocation to either the intervention or control arm. Investigators conducting qualitative interviews and focus groups with patients in the intervention arm will not be blinded to participant arm allocation but systems will be implemented to avoid clinicians or the trial team becoming aware of allocation status for individual participants. [See *Appendix A for study flowchart*].

Participants will receive messages for 26 weeks (approximately six months) from randomisation to final follow-up and remain in the trial for a further 18 months with data collected from their medical record. After the initial screening and eligibility check, informed consent will be obtained.

All participants will be followed-up at the end of the follow-up period post randomisation to collect questionnaire information (same as for baseline) and follow-up measures (same data collected for baseline). [See *Appendix B for a detailed schedule of procedures*].

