### 3.7 Randomisation, blinding and code-breaking

A secure web-based randomisation system will be provided by the Oxford Primary Care Clinical Trials Unit (PC-CTU) using the Sortition software programme. Participants will be allocated to one of the two arms: Intervention Group - usual care with the support of a mobile based intervention or Control Group - usual care with the addition of non-health related messages on a 1:1 basis. Allocation will be carried out using a non-deterministic minimisation algorithm to ensure intervention groups are balanced for important baseline prognostic and other factors: study site, age ( $<65/\geq 65$  years), gender (M/F), duration of diabetes ( $<5/\geq 5$  years), number of medications ( $<5/\geq 5$ ).

If the web-based randomisation system is not accessible, allocation will be carried out following emergency randomisation procedures outlined in the trial working instructions.

Participant allocation will not be formally blinded to healthcare professionals but to avoid contamination around outcome measurement no records of allocation outwith the trial database will be made. As this is a low risk feasibility trial, unblinding procedures are unlikely to be needed. However, in the event of a participant's clinical condition necessitating breaking the code, this will be done according to the relevant PC-CTU SOP or trial specific working instruction and the group allocation will be sent to the chief investigator, site principal investigator or patient's GP.

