#### **3.8.1 Baseline assessment procedures**

After eligibility is confirmed and consent has been taken, the following procedures will take place:

- Contact details will be collected on the phone, or online and will be updated where there is information missing from previous contacts.
- Participant completion of baseline questionnaires. These are:
  - MARS self-report scale (Questions about using your medicines)
  - EQ-5D-5L (Health status EQ-5D-5L)
  - A measure based on health psychology theory and the technology acceptance model. (Ideas and concerns about your diabetes treatment)
  - Healthcare utilisation record (Health services use)
  - Specific questions about experience of diabetes education, presence of a carer and their role in dose administration, duration of diabetes, if the pharmacy used by the participant automatically requests patient's medication from surgery, self-reported level of education, smoking, age, gender, ethnicity, NHS number, Date of Birth, familiarity with mobile phones and computers, and details of current mobile phone including contract.

All self-report data will be collected either on paper forms or electronically.

Participants will be contacted at least 48 hours after they have been provided with their baseline forms to confirm they have received them.

If the forms have not been submitted or received by the trial team 7-14 days from the date they were sent by the team, further contacts will be made.

- The following baseline measures will be obtained from the participant's medical record and provided to the trial team. For the period of 15 months prior to recruitment: HbA1c,

systolic and diastolic blood pressure, total and HDL cholesterol, weight, height, current medication and prescriptions for diabetes drugs (glucose lowering, blood pressure lowering and lipid lowering. Previous occurrence of myocardial infarction, stroke, Transient Ischemic Attack (TIA), heart failure, peripheral vascular disease and renal failure. Data collection will be through one of the following routes: provision of a medical summary by the GP practice team, or a baseline CRF completed by a nurse or facilitator or a trial team member visiting the surgery.

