## 6 STATISTICS

### 6.1 Description of Statistical Methods

The analysis will be carried out once the final patient has completed their 26-week follow up. An intention to treat approach will be used, where all participants randomised will be included in the group to which they were allocated, regardless of intervention received. The results of the primary and secondary objectives will be presented descriptively using proportions and 95% confidence intervals.

The primary outcome will be the number of patients recruited and randomised as a proportion (with 95% confidence interval) of the target recruitment number.

Secondary outcomes, including loss to follow up (%), withdrawals (%) and completeness of data collection for various outcomes (%), will be presented overall and separately by treatment group.

Exploratory outcomes (changes in primary and secondary measures to be used in the main trial) will be analysed using an intention to treat approach. Continuous outcomes will be analysed using an analysis of covariance adjusting for minimisation factors. Results will be presented as a difference in means with 95% confidence interval. Binary outcomes will be analysed in a similar way using log binomial regression models (adjusting for minimisation factors). Results will be presented as relative risks with 95% confidence intervals.

A detailed statistical analysis plan will be prepared prior to data lock.

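### The ANCOVA in section 6.1 does not list the baseline value of the outcome as a covariate and does not say whether the 26-week value or the change is analysed; this costs precision in the exploratory estimates

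*Protocol*

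**What the plan says.** Section 6.1 covers the continuous exploratory outcomes in one sentence: "Continuous outcomes will be analysed using an analysis of covariance adjusting for minimisation factors". The effect measure follows: "Results will be presented as a difference in means with 95% confidence interval".

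Section 3.7 defines the minimisation factors. The algorithm is to keep the arms "balanced for important baseline prognostic and other factors: study site", then age (split at 65 years), gender, duration of diabetes (split at 5 years) and number of medications (split at 5). No outcome measured at baseline is in the list.

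The form of the outcome is described loosely. Section 6.1 speaks of "Exploratory outcomes (changes in primary and secondary measures to be used in the main trial"), and the table in section 2.1 gives the evaluation as "Differences between time points obtained from baseline to 26 weeks". Neither says what stands on the left-hand side of the model.

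Baseline data are planned. Section 3.1 says participants are followed up "to collect questionnaire information (same as for baseline) and follow-up measures (same data collected for baseline"). Sections 3.8.1 and 3.8.2 schedule the adherence scale, the EQ-5D-5L and the psychology and technology acceptance measure at both times. For the clinical values, section 3.8.1 says "The following baseline measures will be obtained from" the medical record, covering the 15 months before recruitment. Section 6.1 ends by promising a detailed statistical analysis plan before data lock.

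**The concern.** For a measure taken before and after randomisation, the baseline value is usually the best single predictor of the follow-up value. The stated covariates do not include it, and none of the clinical or questionnaire outcomes is balanced by the minimisation.

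Two things are at stake. The first is precision: the between-arm differences would carry wider intervals than the collected data allow. The second is chance baseline imbalance, which the stated model handles badly whichever dependent variable is meant.

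Section 1.4 says the trial is meant to inform the design of a later trial, and these outcomes are that trial's own measures. If their residual variance were carried into a main trial that adjusts for baseline, it would be too large.

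**Working it through.** **The plan's own figure.** Section 6.2 gives 73.8% to 85.3% for 80% follow-up in 200 participants. The exact (Clopper-Pearson) interval for 160/200 is 73.78% to 85.31%, so the figure reproduces. It does not depend on the covariates in 6.1.

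**Inputs from the protocol**
- 100 per arm, 80% followed up, so n = 80 per arm (section 6.2).
- Difference in means with a 95% interval, so z = 1.96 (section 6.1).

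**Assumptions, not in the protocol**
- Outcome SD equal at both times and set to 1, so results are in SD units.
- Baseline/follow-up correlation r from 0.3 to 0.8, with 0.5 to 0.7 as the central range. It should be read as the correlation left after the minimisation factors.

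**Formulas for the interval half-width**
- 26-week value, no baseline covariate: 1.96 × √(2/n) = 1.96 × √(2/80) = 0.310.
- Change, no baseline covariate: 0.310 × √(2(1 − r)).
- Baseline as covariate: 0.310 × √(1 − r²).

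The first model fixes the slope on baseline at 0 and the second fixes it at 1. The third estimates it.

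| r | 26-week value | Change | With baseline | Narrowing vs 26-week value | Narrowing vs change |
|---|---|---|---|---|---|
| 0.3 | 0.310 | 0.367 | 0.296 | 4.6% | 19.4% |
| 0.5 | 0.310 | 0.310 | 0.268 | 13.4% | 13.4% |
| 0.7 | 0.310 | 0.240 | 0.221 | 28.6% | 7.8% |
| 0.8 | 0.310 | 0.196 | 0.186 | 40.0% | 5.1% |

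The percentage narrowing does not depend on n. A simulation with 80 per arm, five two-level factors in every model and r = 0.3, 0.5 and 0.7 (2,000 runs each) agreed with these formulas.

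**Equivalent sample size**
- Against the 26-week value the variance ratio is 1 − r²: 200/0.75 = 267 at r = 0.5 and 200/0.51 = 392 at r = 0.7.
- Against the change it is (1 + r)/2: 200/0.75 = 267 at r = 0.5 and 200/0.85 = 235 at r = 0.7.

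**Chance imbalance.** At 80 per arm the baseline difference between arms has an SD of √(2/80) = 0.158. A difference d shifts the estimate by r × d if the 26-week value is analysed and by −(1 − r) × d if the change is analysed. For d = 0.1 and r from 0.5 to 0.7 that is +0.05 to +0.07, or −0.05 to −0.03. With baseline in the model the shift is about zero.

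**Residual variance passed on.** Relative to the baseline-adjusted model it is too large by 1/(1 − r²), which is 1.33 to 1.96 for r from 0.5 to 0.7. For a change score the factor is 2/(1 + r), which is 1.33 to 1.18.

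**The case against.** The strongest reply is that this belongs to the analysis plan still to come. Section 6.1 does not say the minimisation factors are the only covariates. Those factors are all categorical as listed, so calling the model an analysis of covariance fits with a continuous baseline covariate being intended. This stands in part: that baseline is excluded is an inference from a named list. But the protocol has gone beyond silence. It chose a model and named its covariates, and nothing elsewhere adds the baseline value. An analysis plan that follows the text would omit it.

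Four stronger readings are tempting, and the protocol does not support them:

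- *The 13% to 29% gain applies in any case.* It applies only if the 26-week value is analysed. Because the outcomes are described as changes, the other reading is at least as natural, and there the gain is 13% to 8% and falls as the correlation rises.
- *Imbalance is simply left in, or the comparison is biased.* For a change score it is over-corrected, with the opposite sign. Under randomisation neither model is biased on average; the shift is conditional on the imbalance that occurs.
- *Every outcome has a usable baseline.* The clinical values come from routine records, whose completeness is itself a secondary outcome (sections 2.1 and 2.2.2). A medication possession ratio may have little history when entry requires a drug started or changed within three months (section 3.4.1.1).
- *The main trial's sample size will rest on these SDs.* No section says so. It is a fair inference from section 1.4, and the adjusted SD could be computed from the same data anyway.

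**Conclusion.** The point holds as a recommended improvement. The stated covariates omit the baseline value, the dependent variable is not fixed, and no correlation in the range examined favours the model as written under either reading.

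The central size, for r from 0.5 to 0.7, is an interval 13% to 29% narrower for the 26-week value or 13% to 8% narrower for the change. This rests on the assumed correlation and on equal SDs at the two times. Missing baselines would reduce the gain.

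The reach is limited. Primary and secondary results are descriptive proportions and the sample size rests on follow-up precision, so neither changes. Only the exploratory between-arm estimates, and whatever is taken from them for the main trial, are affected.

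**What to change.** In section 6.1, replace the sentence on continuous outcomes with wording such as: *analysis of covariance of the 26-week value, adjusting for the baseline value of that outcome where collected and for the minimisation factors*. This also settles the dependent variable, and the change wording in sections 2.1 and 6.1 should be aligned with it.

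Add a simple rule for missing baselines, such as mean imputation or a missing-indicator term, so that randomised participants with a follow-up value are not dropped. Name any outcome without a usable baseline, the medication possession ratio being the likely one, and analyse it with the minimisation factors alone.

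Report the residual SD and the baseline/follow-up correlation for each outcome to inform the main-trial design.

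The cost is one clause in 6.1 and the matching text in the analysis plan. No new data are needed. The small downside is the handling of incomplete record-based baselines.

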### 6.2 The Number of Cohort 1 Participants

With 200 participants (100 in each group) the feasibility trial is powered to detect 80% follow up within 95% confidence intervals of 73.8% to 85.3%.

### 6.3 The number of Cohort 2 Participants

No formal sample size calculation is required for this Cohort. We aim to recruit between 12 and 30 healthcare professionals based on considerations of data saturation.

## 7 DATA MANAGEMENT

### 7.1 Source Data

Source documents are where data are first recorded, and from which participants' CRF (paper or electronic) data are obtained. These include, but are not limited to, hospital records (from which medical history and previous and concurrent medication may be summarised into the CRF), clinical and office charts, laboratory and pharmacy records, diaries, microfiches, radiographs, and correspondence.

CRF entries will be considered source data if the CRF is the site of the original recording (e.g. there is no other written or electronic record of data). All documents will be stored safely in confidential conditions. On all trial-specific documents, other than the signed consent, the participant will be referred to by the trial participant number/code, not by name.

## 8 Access to Data

Direct access will be granted to authorised representatives from the Sponsor, host institution (University of Oxford) and the regulatory authorities to permit trial-related monitoring, audits and inspections. To ensure data transparency, the trial will be registered on the International Standard Randomised Controlled Trial Number (ISRCTN) registry before the first participant is recruited.

### 8.1 Data Recording and Record Keeping

All trial data where feasible will be entered onto electronic CRFs directly on the trial clinical database. This clinical database will be built and managed by the PC-CTU in line with the PC-CTU SOPs and will hold and allow data management of all data points required to conduct the final analysis. The clinical database will be built on an externally validated secure web-based platform allowing for data tracking by use of date stamped audit logs. In this database, participants will be identified only by a unique trial number to protect from bias and ensure the participant's confidentiality.

Participant identifiable information will be stored in a separate encrypted, secure database, only accessible by trial team members with member-specific log-ins. Participant contact information will be deleted and securely purged from the system six to twelve months after the study has finished.

Paper CRFs will be completed if needed, i.e. if the system is updated and is temporarily unavailable or a participant have opted to complete the data requested on paper. The participants will be identified by a unique trial specific number. The name and any other identifying details will NOT be included in any trial data electronic file or paper CRF.

The study protocol, documentation, data and all other information generated will be held in strict confidence. No information concerning the study, or the data will be released to any unauthorised third party, without prior written approval of the sponsor. A clinical data manager will be assigned to the trial supervised by senior members of the Oxford PC-CTU and PC-CTU SOPs will be followed.

The intervention tested in this trial includes linkage of limited data (medications, appointments, blood test results) from the GP clinical systems to an NHS based computer for the purpose of delivering reminders and prompts to patients when medication may not have been prescribed as planned. This data will be transferred from GP computer systems and securely stored in an NHS compliant computer system. Agreements will be in place between the data supplier, the data processor and individual practices (data owner) setting out responsibilities for the secure handling of this data. This data will only be accessed by members of the research team holding honorary NHS contracts for the purposes of system maintenance. This data will not be accessed, used or stored for secondary use.

All interviews will be recorded using a digital recorder and participants will be asked to consent to this as part of the informed consent process. Written notes will not be made during the interview. Interviews will be uploaded from the digital recorder following the interview, checked and deleted from the recording device. Audio data will be saved on a password-protected university network computer. Interviews will be encrypted before being sent for transcription using the University's secure file-transfer service. Upon receipt, transcripts will be checked for accuracy and anonymised. Transcripts will be password protected and saved on a password-protected university network computer.

## 9 QUALITY ASSURANCE PROCEDURES

The trial will be conducted in accordance with the current approved protocol, Good Clinical Practice (GCP), relevant regulations and PC-CTU standard operating procedures.

Regular monitoring will be performed according to GCP. Data will be evaluated for compliance with the protocol and accuracy in relation to source documents. Following written standard operating procedures, the monitors will verify that the trial is conducted, and data are generated, documented and reported in compliance with the protocol, GCP and the applicable regulatory requirements.

### **9.1 Trial Management Group**

The Trial Management Group (TMG) will be responsible for the monitoring of all aspects of the trial's conduct and progress and will ensure that the protocol is adhered to and that appropriate action is taken to safeguard participants and the quality of the trial itself. The TMG will be comprised of individuals responsible for the trial's day-to-day management (e.g. the CI, trial manager, statistician, data manager) and will meet regularly throughout the course of the trial.

### **9.2 Trial Steering and Data Monitoring Committees**

This trial is a feasibility study and as such will not have a Trial Steering Committee (TSC) or Data Monitoring Committee (DMC). In preparation for a full-trial an independent Trial Steering Committee will be convened to review progress and provide advice to the investigators about all aspects of the future trial.

